#### Post-intervention period outcomes

Using similar mixed effects models, we will estimate changes over time and differences between exercise delivery groups in FACT-F and 6MWT during the 6-month post-intervention period, covering 3 assessment points (end of intervention, 3 months post-intervention, and 6 months post-intervention).

To give a quantitative overview of changes between and within groups over the entire 12 months, all study outcomes will be assessed using these same types of linear mixed effects models. By examination of estimated model parameters and their 95% confidence intervals, we can assess whether changes over time are similar between groups and whether differences between groups at any given time are clinically important.

#### Adherence

Several analyses will be used to assess adherence to the exercise programs and the relationship of adherence to both time and potential predictors. Adherence will be defined as a binary variable for the primary analysis, which uses accelerometry to measure MVPA. We will assess adherence over 4 distinct periods: 0–3 months, 3–6 months, 6–9 months and 9–12 months, so that each subject has up to 4 observation periods for adherence-based analyses. Our first analysis of adherence will simply be the calculation of percentages adhering in each group in each of the 4 time windows. Chi-squared or Fisher’s exact tests will compare adherence across groups within each of the time windows. All further analyses will be done on the sequence of 4 adherence measures on each subject using a generalized estimating equation (GEE) logistic regression model with an AR1 correlation structure.

Predictors of adherence will be examined at the exosystem, mesosystem, and microsystem levels using specific questionnaires as detailed earlier. These will be considered for inclusion in models examining each of the adherence variables separately. Mediation/moderation analyses will be explored based on the primary findings.

#### Cost-effectiveness

We will conduct a within-trial cost utility analysis using standard methods, focusing on interventions directly evaluated in the trial from both payer and societal perspectives. We will adopt two time horizons: the trial (12 months) and the lifetime of the trial cohort. Outcomes will be reported as quality-adjusted life years (QALYs) and cumulative costs, in undiscounted 2017 Canadian dollars.

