##### Costing and utility outcomes

To allow cost-effectiveness analysis, both the EQ-5D-5 L and a patient costs diary will be used. The EQ-5D-5 L is a well-validated, widely used, generic, off-the-shelf preference instrument that measures patient utilities across 5 dimensions of health (mobility, self-care, usual activities, pain/discomfort, and anxiety/depression) [153, 154]. It was originally known as the EuroQol, and has been widely used throughout the world in both clinical investigations and health policy determinations [155]. A total of 3125 unique combinations of scores across the 5 levels of each of 5 dimensions can be generated, each of which can be converted into a utility score based on population-weighted responses from either a United Kingdom-based population cohort or a United States-based cohort [154]. It can be completed in 5 min.

Resource utilization, out-of-pocket costs, and productivity costs will be estimated using a patient cost diary that we have used in prior PC studies, adapted for this study based on patient feedback and response analysis in the phase II trial. More specifically, the patient cost diary will capture: i) hospitalizations/medical events; ii) physician/other health professional services including hospitalizations and outpatient diagnostic tests; iii) drugs, including drug costs unrelated to ADT; iv) equipment costs; v) community services and home care; vi) productivity costs; vii) exercise-specific costs; and viii) out-of-pocket costs.

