#### Outcomes

Quality-adjusted life years (QALYs) will be estimated based on patients’ responses to the EQ-5D-5 L questionnaire [174] collected at each assessment. The EQ-5D-5 L provides a description of a patient’s health state, to which a utility score derived from a set of preference weights measured in a representative sample of the Canadian population can be applied. The EQ-5D-5 L weighted utility scores at each time-point will be used to estimate QALYs following standard procedures [175–177].

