#### Analysis

Cumulative costs and QALYs for each trial arm will be estimated and compared in order to calculate the incremental cost utility ratio, and incremental Net Health Benefit. Censoring for both outcomes will be handled through inverse probability weighting [178, 179].

We will evaluate uncertainty and estimate confidence intervals around the estimates, using both deterministic and probabilistic methods. We will account for correlation between costs and health outcomes using appropriate bivariate methods. Cost-effectiveness acceptability curves (CEACs) will be used to graphically represent the probability that the intervention would be cost-effective for thresholds of $20,000, $50,000, and $100,000 per QALY gained (multiple thresholds for sensitivity analyses). Reporting will follow the Consolidated Health Economic Evaluation Reporting Standards (CHEERS) statement [180].

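### Costs are to be reported undiscounted with no exception for the lifetime horizon, and no discounting rule is given for QALYs, so the lifetime cost-utility results may be distorted

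*Protocol article*

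**What the plan says.** Four statements in the protocol article bear on this point.

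- **Type of analysis** (Statistical analysis, Cost-effectiveness): "We will conduct a within-trial cost utility analysis using standard methods".
- **Horizons** (same section): "We will adopt two time horizons: the trial (12 months) and the lifetime of the trial cohort".
- **Reporting rule** (same section, the next sentence): "Outcomes will be reported as quality-adjusted life years (QALYs) and cumulative costs, in undiscounted 2017 Canadian dollars". The lifetime horizon is not exempted.
- **Use of the results** (Analysis, under Cost-effectiveness): an incremental cost-utility ratio and an incremental Net Health Benefit are to be calculated. Acceptability curves will show "the probability that the intervention would be cost-effective for thresholds of $20,000, $50,000, and $100,000 per QALY gained".

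The economic analysis is the third of the primary aims listed at the end of the Background. It compares both exercise programmes and usual care.

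On utilities, Costing and utility outcomes says that EQ-5D-5L states can be converted with "population-weighted responses from either a United Kingdom-based population cohort or a United States-based cohort". The Outcomes part of the cost-effectiveness section instead refers to "a set of preference weights measured in a representative sample of the Canadian population can be applied", and says that the weighted scores will be used to estimate QALYs.

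**The concern.** A rule against discounting suits a 12-month horizon and does not suit a lifetime one. The interventions run for 6 months, so most programme spending falls in year 1. Any lifetime difference in QALYs, or in later health care costs, would accrue over the following years. The balance between early and late amounts then depends on how time is valued, and the results are to be judged against fixed dollar-per-QALY thresholds.

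The rule fixes this for costs and is silent for QALYs. If QALYs are also left undiscounted, time preference drops out of the lifetime analysis. If QALYs are discounted and costs are not, numerator and denominator of one ratio follow different rules. The sentence is unsatisfactory on either reading.

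The label adds to the difficulty. Assessments end at 12 months, so lifetime results cannot be within-trial. They need extrapolation, and that is where discounting matters.

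**Working it through.** The article gives no economic result, discount rate, survival figure or utility value, so there is no published figure to reproduce. The calculation below shows only how much the rule could matter.

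**Assumed inputs, none from the article:** annual rates r of 1.5%, 3% and 5%; a constant annual difference lasting T years; year 1 undiscounted.

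**Formula.** The discounted total of one unit per year is S = Σ (1+r)^−t for t = 0 to T−1. The undiscounted total is T. The excess is T/S − 1.

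| T (years) | r = 1.5% | r = 3% | r = 5% |
|---|---|---|---|
| 1 | 0% | 0% | 0% |
| 5 | 3.0% | 6.0% | 10.0% |
| 10 | 6.8% | 13.8% | 23.3% |
| 15 | 10.8% | 22.0% | 37.6% |
| 20 | 14.8% | 30.5% | 52.8% |

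For example, at T = 10 and r = 3%, S = 8.786 and 10/8.786 − 1 = 13.8%. The row for T = 1 confirms that the 12-month horizon is unaffected.

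**Effect on the ratio: three cases over 10 years**

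1. *Cost in year 1, QALY gain spread over time.* Assume an extra $1,000 in year 1 and 0.005 QALY gained per year. Undiscounted, the ratio is 1,000/(0.005 × 10) = $20,000 per QALY. With QALYs discounted it is $21,366, $22,763 and $24,668 at the three rates. The inputs were chosen to sit on the lowest threshold, so the crossing shows sensitivity and is not a forecast. Discounting dollars changes nothing here, because all the cost falls in year 1. The whole effect comes from the QALYs.
2. *Costs and QALYs with the same time profile, both treated alike.* S cancels, so the ratio is unchanged. Incremental cost, incremental QALYs and Net Health Benefit still scale with S/T.
3. *Same time profile, but costs undiscounted and QALYs discounted.* The ratio is multiplied by T/S, which is 1.068, 1.138 and 1.233.

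**Net Health Benefit in case 1 at the $20,000 threshold.** Undiscounted it is 0.05 − 1,000/20,000 = 0. At 3% it is 0.005 × 8.786 − 0.05 = −0.006 QALY.

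**Direction.** Reverse the signs in case 1, so that one arm saves $1,000 in year 1 and loses 0.005 QALY per year. The saving per QALY lost rises from $20,000 undiscounted to between $21,366 and $24,668. Discounting then favours the cheaper arm. The sign therefore depends on which arm costs more and which gains QALYs.

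**Value sets.** No utilities are given, so no effect can be computed. The measures section says what conversion is possible, while the analysis section ties the weighted scores to the QALY calculation.

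**The case against.** The strongest objection is that the word undiscounted qualifies the dollars. A reader might infer that lifetime QALYs are stated to be undiscounted, but the article does not say so; QALY discounting is simply unstated. This stands. It also means that the percentages above rest on the unstated half whenever costs fall in year 1.

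Second, a constant difference for 10 years or more sits badly with the article's own Background. There, about half of the general population stop exercising after 6 months, stopping loses the benefits, and two studies found quality-of-life gains diminished 4 to 6 months after the intervention. This stands as well. An effect confined to the first year or two would make discounting of QALYs almost irrelevant.

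Third, a reader might conclude that the lifetime results will be wrong, or will flatter exercise. The documents do not support that. Undiscounted totals are valid as description. The group arm is described as needing more resources, so the comparison between arms could move either way.

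Fourth, a reader might say that two competing value sets will yield two QALY results. That goes too far. The United Kingdom and United States cohorts appear in a general description of the instrument, and only the Canadian weights are linked to the QALY calculation.

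Finally, an article may leave model details to a fuller plan, and this one refers to standard methods and to CHEERS reporting. That would excuse an absent rate. It does not excuse a rule that is stated and covers a horizon it does not suit.

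**Conclusion.** The point holds in a limited form. The article fixes undiscounted dollars for both horizons and gives no QALY rule. The 12-month results are unaffected. Lifetime ratios, Net Health Benefit and acceptability curves may be distorted, either because time preference is ignored throughout or because costs and QALYs are treated differently.

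The possible size is 7% to 23% on a constant 10-year stream at assumed rates of 1.5% to 5%, and 3% to 10% if the difference lasts 5 years. These figures rest on assumed rates and a persistent difference, and the direction is undetermined. The matter deserves correction because the economic analysis is a primary aim and its results are set against funding thresholds. It does not touch the co-primary outcomes, randomization or data collection. The value-set wording is a minor inconsistency.

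**What to change.** - Limit the undiscounted rule to the 12-month horizon.
- For the lifetime horizon, discount both costs and QALYs after year 1 at one common prespecified rate, with 0% and a higher rate as sensitivity analyses.
- Describe the lifetime analysis as a model-based extrapolation and keep the within-trial label for the 12-month analysis.
- Minor: in Costing and utility outcomes, name the Canadian weights that the later Outcomes section uses.

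The cost is a few sentences and one parameter in the economic model, and no new data are needed. The downside is that lifetime figures will change and may become less favourable to one arm. The 0% sensitivity analysis would keep the undiscounted result visible.

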#### Costs

We will estimate costs for all health care use in both arms, including:i).hospitalizations/medical events;ii).physician/other health professional services including outpatient diagnostic tests;iii).drugs, including drug costs unrelated to ADT;iv).equipment costs;v).community services and home care;vi).productivity costs;vii). exercise-specific costs;viii). out-of-pocket costs.

The intervention will be costed by estimating the value of time of those administering the intervention, facility-use costs, and device/ equipment costs, amortized over an appropriate period. Resource utilization, out-of-pocket costs, and productivity costs will be estimated using a patient cost diary. We will assess economically relevant health status using the EQ-5D-5 L at each time point [153, 154]. Valuation will be conducted using province-specific estimates when possible (e.g. schedule of physician benefits, cost per weighted case) and standard methods (e.g. provincial schedule of benefits, resource intensity weights and average cost per weighted case) [170–172]. Productivity losses will be valued both by the human capital (with adjustment for labour force participation) and friction cost methods [173].

#### Outcomes

Quality-adjusted life years (QALYs) will be estimated based on patients’ responses to the EQ-5D-5 L questionnaire [174] collected at each assessment. The EQ-5D-5 L provides a description of a patient’s health state, to which a utility score derived from a set of preference weights measured in a representative sample of the Canadian population can be applied. The EQ-5D-5 L weighted utility scores at each time-point will be used to estimate QALYs following standard procedures [175–177].

#### Analysis

Cumulative costs and QALYs for each trial arm will be estimated and compared in order to calculate the incremental cost utility ratio, and incremental Net Health Benefit. Censoring for both outcomes will be handled through inverse probability weighting [178, 179].

We will evaluate uncertainty and estimate confidence intervals around the estimates, using both deterministic and probabilistic methods. We will account for correlation between costs and health outcomes using appropriate bivariate methods. Cost-effectiveness acceptability curves (CEACs) will be used to graphically represent the probability that the intervention would be cost-effective for thresholds of $20,000, $50,000, and $100,000 per QALY gained (multiple thresholds for sensitivity analyses). Reporting will follow the Consolidated Health Economic Evaluation Reporting Standards (CHEERS) statement [180].

## Discussion

PC is the most common cancer in men. ADT is widely used to treat men with PC. It prolongs survival and slows disease progression but at the cost of numerous adverse effects. Exercise has been shown to mitigate and reverse many ADT-associated adverse effects, yet it is not widely available or implemented. To date, no study has examined which delivery model of exercise is most effective at producing these results or which are sustainable in the longer term, nor have studies examined the costs of these delivery approaches. These gaps in translational research must be addressed before exercise can be integrated into standard care for this population. The proposed multi-centre phase III trial aims to definitively answer these 3 questions (efficacy, long-term adherence, cost-effectiveness). Thus, this trial has tremendous empirical and practical relevance for men receiving ADT, and its findings should provide clear data on the value of implementing exercise programs for men on ADT. Additionally, our findings on psychological predictors of adherence will serve as the basis for future theory-based intervention studies designed to enhance long-term adherence to exercise. As such, the findings from the proposed study will serve as a foundation in the evidence-based clinical integration of exercise in this population.

As detailed elsewhere [113] (manuscript submitted), the current protocol is similar to our prior phase II trial in many ways, but with four key differences as informed by the results of the phase II trial [101]. First, the 1:1 supervised exercise arm has been eliminated. Second, all participants in the home-based arm will receive Fitbits to provide real-time, practical feedback on step counts as an easy to understand summary of physical activity performed. Fitbits were not provided in the phase II trial. Third, health coaches will meet once monthly in person with each participant in the home-based arm. In the prior trial, there was no in-person meeting. Fourth, to reduce participant burden in terms of outcome measures, and to incorporate emerging data on neighborhood walkability measures, our outcomes were streamlined with the Neighborhood Walkability Scale being substituted by postal code capture to facilite neighborhood walkability analysis, substitution of the PNSF for Relatedness to Others in Physical Activity Scale (ROPAS), and administration of the HCCQ at baseline only. These modifications should ensure the trial incorporates current evidence from published studies and our own phase II RCT, and positions it to provide invaluable data addressing the value of different exercise delivery models, determine the cost-effectiveness of exercise among men on ADT, as well as generate important insights into long-term adherence and predictors of adherence.

## Abbreviations

6MWT: Six-minute walk test
ADT: Androgen Deprivation Therapy
AED: Automated external defibrillator
BIA: Bioelectrical impedance analysis
BMD: Bone mineral density
BP: Blood Pressure
BREQ-2: Behavioral Regulations in Exercise Questionnaire – 2
CEP: Certified Exercise Physiologist
CHEERS: Consolidated Health Economic Evaluation Reporting Standards
CPR: Cardiopulmonary resuscitation
CSEP: Canadian Society for Exercise Physiology
CSEP-PATH: Canadian Society for Exercise Physiology – Physical Activity Training for Health
CTCAE: Common Terminology Criteria for Adverse Events
DXA: dual x-ray absorptiometry
EQ-5D: EuroQol 5 dimensions of health scale;
FACT-F: Functional Assessment of Cancer Therapy - Fatigue
FACT-G: Functional Assessment of Cancer Therapy - General
FACT-P: Functional Assessment of Cancer Therapy - Prostate
FITT: Frequency, Intensity, Time, Type
GEE: Generalized estimating equation
GLTEQ: Godin Leisure Time Exercise Questionnaire
HbA1c: Glycosylated hemoglobin
HCCQ: Health Care Climate Questionnaire
HR: Heart Rate
HRreserve: Heart rate reserve
MVPA: Moderate to Vigorous Physical Activity
PAB: Planning, Attitudes, & Behaviour questionnaire
PC: Prostate Cancer
PM: Princess Margaret Cancer Centre
PNSF: Psychological Need Support and Frustration Scale – Relatedness Items
PSA: Prostate-specific antigen
QALY: Quality-adjusted life years
QOL: Quality of Life
RC: Research Coordinator
RCT: Randomized Controlled Trial
RKin: Registered Kinesiologist
RPE: Rated perceived exertion
SRH: Scarborough and Rouge Hospital – Centenary site
SRHC: Southlake Regional Health Centre
TBCC: Tom Baker Cancer Centre
WC: Waist circumference
